#### 2.7.4. Simulation Architecture, Latency, and Availability

TN uses a hybrid architecture. The mobile app performs on-device functions (UI, local state, lightweight redaction, and caching), while LLM inference for coach–athlete simulations is executed server-side via a managed API. Before any request is sent, the client strips potentially identifying tokens (names, school references, contact details) from coach inputs; no student-authored text is transmitted to LLM services. Requests are transmitted only in de-identified form and are not retained by vendors or used for model training.

Prior to any request being transmitted to external LLM APIs, TN applies a lightweight, deterministic client-side redaction layer designed to remove potentially identifying tokens from coach-authored inputs. This process uses a rule-based filtering pipeline that detects and strips common personally identifying patterns (e.g., names, email addresses, phone numbers, school identifiers, and location references) using regular expressions and fixed lexical rules before serialization of the request payload. Redaction is performed synchronously on-device, and only the sanitized text is eligible for transmission.

To ensure reliability, the redaction module was iteratively tested during development using synthetic inputs containing embedded identifiers to verify consistent removal prior to API calls. In addition, request payloads sent to LLM endpoints are logged locally in redacted form during development and staging environments to support auditing and verification that no identifying content is transmitted. While no automated system can guarantee perfect de-identification, this layered, client-side approach substantially reduces the risk of inadvertent disclosure and aligns with the platform’s design principle of minimizing data exposure by default.

### 2.8. Measures

Demographic characteristics and student-athlete outcomes will be measured using online surveys at the beginning, middle, and end of the season. Demographic characteristics include the ages, genders, races/ethnicities, and types of sports of coaches and student-athletes. Student-athletes will be asked to self-report their physical activity (over the past 7 days): “On how many days were you physically active for a total of at least 60 min per day? (Add up all the time you spent in any kind of physical activity that increases your heart rate or makes you breathe hard some of the time.)”

In addition, student-athletes will be asked to self-report four brief mental-health–related items adapted from validated adolescent screening tools. Items include the following:(1)“When you feel sad or hopeless, are there adults that you can turn to for help?” ([Bibr B2-behavsci-16-00268]);(2)“During the past two weeks, how often have you been bothered by feeling nervous, anxious, or on edge?” ([Bibr B19-behavsci-16-00268]);(3)“During the past two weeks, how often have you been bothered by not being able to stop or control worrying?” ([Bibr B19-behavsci-16-00268]);(4)“During the past 12 months, did you ever feel so sad or hopeless almost every day for two weeks or more in a row that you stopped doing some usual activities?” ([Bibr B2-behavsci-16-00268]).

These items are used descriptively to complement standardized scales and provide context for student-athlete well-being ([Bibr B2-behavsci-16-00268]; [Bibr B19-behavsci-16-00268]).

#### 2.8.1. Sport Satisfaction

Student-athlete intrinsic satisfaction in sport participation will be measured through the Sport Satisfaction Instrument (SSI), which consists of two subscales (i.e., satisfaction/fun and boredom). Student-athletes will be asked to rate the extent to which they agree with each of the eight items, using a Likert scale from 1 (Strongly Disagree) to 5 (Strongly Agree). Studies have demonstrated reliability and validity ([Bibr B11-behavsci-16-00268]; [Bibr B21-behavsci-16-00268]).

#### 2.8.2. Sport Motivation

Based on the tenets of SDT, the Sport Motivation Scale-II is an 18-item instrument developed to measure the motivational level of student-athletes ([Bibr B27-behavsci-16-00268]). SMS-II consists of six subscales, including amotivation, external regulation, introjected regulation, identified regulation, integrated regulation, and intrinsic motivation. Student-athletes will be asked to rate on a Likert scale the extent to which the motivations presented to practice sports align with their personal motives. Motivation was assessed using a 7-point Likert scale ranging from 1 (Do Not Agree at All) to 7 (Totally Agree). SMS-II is a valid measure across different studies and socio-cultural contexts ([Bibr B28-behavsci-16-00268]).

#### 2.8.3. Mental Well-Being

The 14-item Warwick–Edinburgh Mental Well-being Scale (WEMWBS) will be used to measure the different aspects of positive mental health of student-athletes ([Bibr B39-behavsci-16-00268]). The WEMWBS covers both hedonic and eudaimonic aspects of mental health, including positive affect, satisfying interpersonal relationships, and positive functioning. Student-athletes will be asked to best describe their experience of each statement over the past two weeks using a 5-point Likert scale from 1 (None of the Time) to 5 (All of the Time). The validation process is described in Tennant and colleagues ([Bibr B39-behavsci-16-00268]).

#### 2.8.4. Burnout

Student-athlete burnout will be assessed by the 15-item Athlete Burnout Questionnaire (ABQ), developed by Raedeke and Smith ([Bibr B32-behavsci-16-00268]). Items are answered on a 5-point Likert scale. Student-athletes will be prompted to reflect on their current sport experiences and rate how often they experienced the feelings identified in each item, using a 5-point Likert scale from 1 (Almost Never) to 5 (Almost Always). The ABQ includes three subscales related to emotional/physical exhaustion, sport devaluation, and reduced sense of accomplishment. The ABQ is supported by various forms of evidence for its validity ([Bibr B12-behavsci-16-00268]).

#### 2.8.5. Coach–Athlete Relationship

The 11-item Coach–Athlete Relationship Questionnaire (CART-Q) will be employed to assess the multidimensional nature of the coach–athlete relationship ([Bibr B17-behavsci-16-00268]). The CART-Q consists of three subscales: commitment, closeness, and complementarity. CART-Q items will be measured on a 7-point scale ranging from 1 (Strongly Disagree) to 7 (Strongly Agree). The CART-Q has been widely used in youth sport studies with sufficient evidence to support its validity and reliability ([Bibr B17-behavsci-16-00268]; [Bibr B42-behavsci-16-00268]).

#### 2.8.6. Autonomy-Supportive Coaching

Seven items relating to the student-athlete’s perceived autonomy-supportive coaching behaviors will be adopted from a previous study ([Bibr B6-behavsci-16-00268]). Student-athletes will be prompted to recall their sport experiences, with a specific focus on autonomy-supportive coaching behaviors during the season, and rate each item from 1 (Strongly Disagree) to 5 (Strongly Agree). Psychometric Instruments are illustrated in [App app1-behavsci-16-00268].

#### 2.8.7. User Interface and User Experience

We will conduct exploratory, semi-structured interviews with a purposive sample of coaches and student-athletes at the end of the season to gather usability and user-experience (UI/UX) feedback on the TN platform. An interview guide developed by the research team (see [App app2-behavsci-16-00268]) will be used.

### 2.9. Data Analysis

Analyses will use linear mixed-effects models (LMMs) estimated via REML to account for nesting (student-athletes within teams within schools) and to accommodate unbalanced repeated measures. Fixed effects will include condition (intervention vs. waitlist control), time (baseline, mid-, and end-season), and their interaction; random intercepts will be specified for team and school. Missing data will be handled by maximum-likelihood under MAR; if attrition exceeds 20%, multiple imputation will be used as a sensitivity analysis. Prespecified covariates include type of sport, gender, grade, and prior mental-health support. Given the pilot nature and very limited clusters, results will emphasize descriptive effect sizes with 95% CIs and ICCs/design effects rather than confirmatory *p*-values; where *p*-values are reported, we will control the false discovery rate (Benjamini–Hochberg) across outcomes.

Because cluster-randomized designs with few clusters are susceptible to chance baseline imbalances, baseline values of each outcome will be included as covariates in all longitudinal models. This baseline-adjusted specification is expected to improve precision and reduce bias attributable to baseline differences between conditions. As a sensitivity analysis, estimates will be examined with and without adjustment for multiple comparisons to evaluate the robustness of observed patterns. These analyses are intended to support transparent interpretation of exploratory findings.

Verbatim transcriptions of coach and student-athlete interviews will be analyzed using rapid content analysis to identify key usability insights, perceived benefits, and improvement opportunities related to the TN platform. The analysis will prioritize efficiency and practical relevance in studies with small samples, maintaining analytic rigor through structured coding and documentation. Two researchers will independently review transcripts, generate preliminary codes, and summarize key points within a shared matrix. Codes will then be grouped into higher-order categories to capture salient patterns in user experience and acceptability ([Bibr B6-behavsci-16-00268]). Findings will be summarized thematically but interpreted as exploratory, descriptive feedback rather than claims of thematic saturation. NVivo 12 ([Bibr B31-behavsci-16-00268]) will be used for data organization and coding.

Trustworthiness will be addressed through multiple strategies: credibility will be strengthened by peer debriefing within the research team and participant validation of summary findings; dependability will be supported through an audit trail documenting analytic decisions; and confirmability will be ensured through a transparent, data-grounded coding process. Thick description of the study context and participant characteristics will promote transferability for similar school-based interventions.

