### 2.3. Sample Size Calculation

The present study is not powered for any confirmatory inference. The targeted roster sizes (approximately 15–25 athletes per team) are sufficient to evaluate feasibility and engagement and to provide preliminary clustering estimates (i.e., intraclass correlation coefficient). We will report these estimates with 95% confidence intervals. Precision will be limited by the small number of teams. Published intraclass correlation coefficient (ICC) values will also inform power for a future cluster-randomized trial.

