If more than 50% of parents or guardians on a selected team decline participation, that team will be replaced by another eligible team from the same school, which will inherit the school’s randomized condition to preserve the integrity of the cluster randomization. No re-randomization will occur at the team level. Parents or guardians of student-athletes in the waitlist control condition will receive similar study information but will be informed that their child(ren) will complete online surveys across the season and gain access to the TN mobile application after the season ends.

For the intervention group, a 30 min online pre-season training will be offered to orient participants to TN, including installation, initial setup, and core functions. Both the intervention and control groups will complete online surveys at three time points: the beginning of the season (baseline), mid-season, and the end of the season. Before each survey, participants will be reminded that their participation is voluntary, that they may withdraw at any time without penalty, and that their responses will be anonymous and not shared with coaches, parents, or school staff.

All survey data will be de-identified and stored on encrypted servers, accessible only to the research team. Coaches will not have access to individual student responses, only to aggregated, anonymized team-level summaries where appropriate. Neither personal-level data will be visible to schools nor to the TN developers.

Within two weeks of the postseason, coaches and student-athletes in the control group will be introduced to TN through a short tutorial and guided installation instructions via email. The study protocol and all related materials will be reviewed and approved by the Institutional Review Board prior to participant recruitment. All procedures will be conducted in accordance with the ethical principles outlined in the Declaration of Helsinki.

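### Section 2.9 names no athlete-level term although athletes are surveyed three times: change-over-time intervals come out too wide, the team ICC slightly high, and dropout driven by the mid-season score is not covered

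*Protocol article*

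**What the plan says.** Section 2.9 (Data Analysis) of the protocol article chooses linear mixed models estimated by REML "to account for nesting (student-athletes within teams within schools) and to accommodate unbalanced repeated measures". Fixed effects are condition, time at three levels including baseline, and their interaction. The random part is given as "and their interaction; random intercepts will be specified for team and school". No athlete intercept and no within-athlete residual covariance is named anywhere in the article.

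Three other statements bear on this:

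- Section 2.4 (Procedure): both groups "will complete online surveys at three time points: the beginning of the season (baseline), mid-season, and the end of the season".
- Section 2.9: "baseline values of each outcome will be included as covariates in all longitudinal models".
- Section 2.9: "Missing data will be handled by maximum-likelihood under MAR", with multiple imputation as a sensitivity analysis only if attrition passes 20%.

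The outputs to be emphasised are effect sizes with 95% confidence intervals, ICCs and design effects. Sections 2.3 and 4 carry the clustering estimates forward to the planning of a later trial.

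**The concern.** The data have measurements within athletes, athletes within teams, and teams within schools. The listed random terms cover teams and schools and skip the athlete. Once team and covariates are accounted for, the fitted model sees three surveys from one athlete as if they came from three athletes. Three kinds of result could be affected:

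- **Intervals.** Research questions 1 to 3 (section 1) ask how change over the season differs between conditions. That is a within-athlete contrast, and its standard error depends directly on the within-athlete correlation.
- **ICC.** Stable differences between athletes that have no term of their own are partly attributed to teams.
- **Missing data.** Likelihood-based handling borrows from an athlete's observed scores only through a modelled correlation. Without one, a mid-season score says nothing about a missing end-season score.

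**Working it through.** The article states no ICC, within-athlete correlation, power or sample-size result, so there is no figure to reproduce.

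**Inputs from the article.** Four teams, two per condition (section 2.4); about 15–25 athletes per team, written m (section 2.3); three waves (section 2.4).

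**Assumptions.** Equal correlation r = 0.5 to 0.7 between any two waves of one athlete within a team; within-team variance 1 in the formulas. The simulations used m = 20, total variance 1 and true team ICC 0.05, so within-team variance 0.95. They left out the school intercept because one school per arm makes it inseparable from condition.

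The baseline rule can be read in more than one way, so three models were compared:

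- *literal*: all three waves as outcome, baseline also a covariate
- *two-wave*: mid and end as outcome, baseline a covariate
- *no covariate*: all three waves as outcome, for reference only

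**1. Condition-by-time contrast (last wave minus first modelled wave).** The true variance per athlete is 2(1−r). The model without an athlete term uses twice its own residual variance.

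- No covariate: residual variance 1. SE ratio = 1/√(1−r) = 1.41 (r = 0.5) to 1.83 (r = 0.7).
- Two-wave: residual variance 1−r². SE ratio = √[(1−r²)/(1−r)] = √(1+r) = 1.22 to 1.30.
- Literal: pooled baseline slope b = (1+2r)/3 = 0.667 to 0.80; residual variance 1−b² = 0.556 to 0.36. SE ratio = √[(1−b²)/(1−r)] = √(0.556/0.5) to √(0.36/0.3) = 1.05 to 1.10.

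Simulation check (240 runs per scenario). With 40 athletes per arm the true SE is √[2(1−r) × 0.95 × (1/40 + 1/40)] = 0.218 at r = 0.5 and 0.169 at r = 0.7.

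| Model | Mean SE, no athlete term (r = 0.5; 0.7) | Ratio to true SE | Mean SE, with athlete term |
|---|---|---|---|
| No covariate | 0.306; 0.305 | 1.40; 1.80 | 0.217; 0.170 |
| Two-wave | 0.265; 0.218 | 1.22; 1.29 | 0.216; 0.167 |
| Literal | 0.228; 0.183 | 1.05; 1.08 | 0.216; 0.168 |

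At r = 0.5, coverage of the nominal 95% interval without the athlete term was 99%, 98% and 97% in that order.

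**2. Average over the post-baseline waves.** After baseline adjustment the mid-to-end correlation that remains is r/(1+r) = 0.33 to 0.41. In the two-wave model with team variance at zero, the SE ratio is 1/√(1 + r/(1+r)) = 0.87 to 0.84. When team variance is estimated, the team intercept takes up the shortfall, and the SE is about right or slightly large in the two-wave and no-covariate models. On the literal reading it stays about 14–19% too small.

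**3. Team ICC.** In the two-wave model the athlete variance that leaks into the team term, as a share of residual variance, is [r/(1+r)]/(2m). This runs from 0.333/50 = 0.007 (r = 0.5, m = 25) to 0.412/30 = 0.014 (r = 0.7, m = 15). Simulated mean ICC at m = 20, without and with the athlete term:

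- Two-wave: 0.0295 and 0.0218 (excess 0.008) at r = 0.5; 0.0238 and 0.0169 (excess 0.007) at r = 0.7.
- Literal: 0.0171 and 0.0036 (excess 0.014) at r = 0.5; 0.0147 and 0.0045 (excess 0.010) at r = 0.7.

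For scale, four teams less two arm means leave 2 degrees of freedom, so a between-team mean square has a standard deviation equal to its mean. Without the covariate, at m = 20 and r = 0.5, this is 0.05 + 0.95 × 2/60 = 0.082. Simulation of that model put the sampling SD of the ICC at 0.06–0.08.

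**4. Dropout that depends on the mid-season score.** About 32% of the TN arm lost before the last wave (about 16% overall, below the trigger for imputation), no true effect, r = 0.5. Bias in the end-of-season arm difference, without and then with the athlete term:

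- No covariate: +0.163 and −0.006 SD.
- Two-wave: +0.072 and −0.011 SD.
- Literal: +0.041 and +0.021 SD.

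Monte Carlo standard errors are 0.013–0.022. A second scenario (30% control and 10% TN dropout, r = 0.5–0.6) gave 0.02–0.07 SD with the covariate.

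**The case against.** The strongest reply is that silence is being read as exclusion. The sentence speaks of athletes nested in teams and of repeated measures, never says that the listed intercepts are the only ones, and the article cites a preregistration that is not at hand. The authors may well intend an athlete term. That stands as to intent. But section 2.9 does not leave the random part open: it lists it, beside the estimator and the fixed effects, and the list does not do what the sentence says the model is for. If an athlete term is intended, the text needs the same correction.

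The reply also limits the size of the point. Three stronger readings might be inferred, and the documents do not support them.

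- *All intervals are wrong, in both directions.* The plan fits a team intercept, and this largely protects arm averages. Without the covariate, simulated model SE against empirical SD for the arm average was 0.290 against 0.288 at true ICC 0.05, and 0.193 against 0.184 at true ICC 0. Intervals that are too narrow arise on the literal reading or when team variance is estimated at zero.
- *The ICC is badly inflated.* Without the baseline covariate, a true 0.05 would read 0.062–0.080. At 20 per team and r = 0.6 it would read about 0.068, giving a design effect of 1 + 19 × 0.068 = 2.29 instead of 1 + 19 × 0.05 = 1.95. Section 2.9 requires the covariate in every longitudinal model, so these figures describe a model that is not planned. The adjusted ICC lies below 0.05 either way and is high only relative to the same model with an athlete term. Nor is a positive estimate at a true ICC of zero mainly this fault: with the athlete term such estimates still averaged 0.009–0.019, because variances cannot go below zero.
- *The missing-at-random claim fails.* It survives if missingness depends only on baseline and the covariates.

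Finally, the article disclaims confirmatory inference. That lowers the stakes but does not remove the point, because intervals and variance components are the outputs it promises.

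**Conclusion.** The point holds in a limited form. As written, section 2.9 leaves the within-athlete correlation beyond the baseline covariate unmodelled, contrary to its stated aim.

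- Condition-by-time intervals are conservative: SEs about 5–10% too large on the literal reading, 20–30% with mid and end as outcomes, and 40–85% if no baseline covariate were used. The post-baseline average can be too narrow in the two situations named above.
- The team ICC is about 0.01 too high relative to the same model with an athlete term, well inside its sampling error with four teams.
- Missing-data handling does not extend to dropout that depends on an observed mid-season score, with bias of about 0.02–0.07 SD under the planned covariate.

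All sizes rest on an assumed within-athlete correlation of 0.5–0.7, equal across waves, and on invented but plausible dropout patterns. The direction for the condition-by-time contrast does not depend on the exact value, as long as the correlation is positive.

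**What to change.** In section 2.9, add to every longitudinal model a random intercept for student-athlete within team, or an unstructured within-athlete residual covariance over the waves that are modelled as outcomes. Define the team ICC as team variance divided by the sum of team, athlete and residual variance from that model, and say that it is conditional on baseline where the baseline covariate is included.

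The cost is one model term and one sentence. No new data are needed, because using each athlete's own baseline as a covariate already requires linked records. The change should be made before the data are analysed.

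It does not cure two separate problems. One school per arm still limits any comparison between conditions. Baseline as both outcome and covariate still distorts the literal model: at r = 0.5, with the athlete term added, the mean SE of its end-of-season arm difference was 0.168 against an empirical SD of 0.203, and about half of the dropout bias remained. Which waves are outcomes should therefore be settled in the same edit.

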### 2.4. Procedure

Coaches and high school student-athletes will be recruited from a purposive sample of two public high schools within a district that reflects a diverse demographic composition. Schools will serve as the unit of randomization and will be randomly assigned to either the TN intervention group or the waitlist control group. Four weeks prior to the start of the season, head coaches will be contacted via email, using the contact information provided by the district athletic director. Following pre-screening to confirm their coaching role, coaches will be invited to complete an online enrollment survey that includes the purpose of the study, its procedures, and an option to opt out. Coaches who consent to participate will be listed under the intervention or control condition. Two teams from each school will then be randomly selected for inclusion, resulting in a total of four participating teams. To prevent potential contamination, both teams from the same school will remain in the same condition, consistent with school-level group assignment. Teams in the intervention group will have access to TN throughout the season, whereas teams in the control group will serve as a waitlist control and receive access after the study is completed.

Parental consent and student-athlete assent will follow IRB-approved procedures appropriate for research with minors. Given that the study involves a non-clinical, educational mobile platform and poses no greater than minimal risk, the research team will seek for a passive (opt-out) parental consent process, consistent with school district research policies.

Parents or legal guardians will receive an informational letter via email two weeks before data collection, describing the study purpose, procedures, confidentiality protections, and voluntary nature of participation. The letter will include both an online opt-out form and contact information for the research team. Those who do not opt out will be considered to have provided consent. Student-athletes will then provide electronic assents prior to participation, with the option to withdraw at any time without penalty.

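### The mixed model in Section 2.9 has no athlete term, so repeated surveys from one athlete are modelled as conditionally independent, which modestly distorts the 95% CIs and the team ICC

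*Protocol article*

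**What the plan says.** Section 2.9 (Data Analysis) chooses linear mixed models fitted by REML "to account for nesting (student-athletes within teams within schools) and to accommodate unbalanced repeated measures". The fixed part is given next: "Fixed effects will include condition (intervention vs. waitlist control), time (baseline, mid-, and end-season), and their interaction". The random part is a closed list: "random intercepts will be specified for team and school". The next paragraph adds that "baseline values of each outcome will be included as covariates in all longitudinal models".

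The data are repeated within athlete. Section 2.4 states: "Both the intervention and control groups will complete online surveys at three time points". There are four teams, two per school and one school per arm, with "approximately 15–25 athletes per team" (Section 2.3). That makes 60 to 100 athletes and up to 180 to 300 survey records.

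On reporting, Section 2.9 says that "results will emphasize descriptive effect sizes with 95% CIs and ICCs/design effects rather than confirmatory" p-values. Section 4 adds that the estimated ICCs and design effects will guide the size of a later, fully powered cluster-randomized trial. No athlete random effect or within-athlete residual covariance is named anywhere in the article.

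**The concern.** The paragraph sets two aims, nesting and repeated measures, but the random effects it names serve only the first. Stable differences between athletes have no variance component of their own. In the fitted model they go partly into the residual and partly into the team variance.

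The intervals are then wrong in two directions. A change within athlete is judged against a residual that contains between-athlete variance, so its SE is too large. A season average, or the effect of an athlete-level covariate such as gender or grade, is judged as if three surveys were three separate athletes, so its SE is too small. The team variance is also inflated, because averaging over a team's athletes leaves more between-team scatter than the model expects. The CIs and ICCs affected are the outputs that the plan says it will emphasise.

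**Working it through.** **Inputs.** From the article: 3 surveys per athlete, 4 teams, m = 15–25 athletes per team (20 used below), baseline outcome as covariate. Assumed, because the article gives no value: exchangeable within-athlete correlation r = 0.4 / 0.6 / 0.8. Within-team variance is scaled to 1. The school intercept is left out, because school coincides with condition. The article states no figure of its own on this point, so there is nothing to reproduce.

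**1. Condition-by-time, model as written.** The baseline score is a covariate with one slope b, while the baseline wave is also a response. Pooled over the three waves, b = (1 + r + r)/3 and the residual variance is 1 − b².
- The model gives a within-athlete change the variance 2(1 − b²). The true variance is 2(1 − r), because the covariate is constant across an athlete's waves and cancels.
- SE ratio = √[(1 − b²)/(1 − r)] = (2/3)√(2 + r).
- Result: 1.03 / 1.08 / 1.12, so the SE is about 3% / 8% / 12% too large.

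Simulation of the same model (team variance 0.05, 600 runs per setting) agrees. Mean SE was 0.251 / 0.213 / 0.157 as written and 0.244 / 0.199 / 0.141 with an athlete intercept, which gives ratios of 1.03 / 1.07 / 1.11.

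**2. Averaged and athlete-level effects, model as written.** Given baseline, the mid- and end-season scores correlate (r − r²)/(1 − r²) = r/(1 + r) = 0.29 / 0.38 / 0.44. The baseline covariate therefore removes only part of the dependence.
- For the sum over three waves, the Y₀ terms cancel (1 + 2r − 3b = 0). The true variance is 2(1 − r)(1 + 2r).
- The model assumes 3(1 − b²) = (4/3)(1 − r)(2 + r).
- SE ratio = √[(2/3)(2 + r)/(1 + 2r)] = 0.94 / 0.89 / 0.85.

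Before any team variance is added, the SE is thus about 6% / 11% / 15% too small. For the between-arm average, the inflated team variance offsets part of this.

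**3. Team variance and ICC, no baseline covariate.** The variance of a team mean contains r/m + (1 − r)/(3m) from athletes and surveys. The model without an athlete term allows only 1/(3m).
- Excess booked to team: r/m − r/(3m) = 2r/(3m).
- At m = 20: 0.013 / 0.020 / 0.027. Over m = 15–25: 0.011 to 0.036.

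Mean estimated team ICC by simulation (m = 20, 4,000 runs per setting):

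| True ICC | Team intercept only | With athlete intercept |
|---|---|---|
| 0 | 0.016 / 0.023 / 0.028 | 0.011 / 0.014 / 0.015 |
| 0.05 | 0.060 / 0.066 / 0.070 | 0.051 / 0.052 / 0.053 |
| 0.10 | 0.101 / 0.104 / 0.112 | 0.092 / 0.090 / 0.094 |

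At a true ICC of 0.05 or 0.10, the gap between the two models is 0.009 to 0.018. At 0.10, the few-team bias pulls both estimates down, so the written model looks less wrong there than it is.

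**4. What the ICC shift means for planning.** With 20 per team, the design effect 1 + 19 × ICC is 1.95 at 0.05, 2.14 at 0.060 and 2.33 at 0.070. That is a sample 10% to 19% larger than needed (2.14/1.95 and 2.33/1.95).

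**The case against.** The strongest reply has four parts.

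- **The baseline covariate does much of the work.** This stands. Without that covariate the condition-by-time SE would be 1/√(1 − r) = 1.29 / 1.58 / 2.24 times too large. A reader might quote those ratios, but Section 2.9 puts baseline in every longitudinal model, so they do not describe this plan. In the 600-run simulation, the written model's nominal 5% test of condition-by-time rejected 4.2% / 3.3% / 5.5%: close to nominal or mildly conservative.
- **An athlete term could make that test liberal.** The same runs gave 4.7% / 4.8% / 8.5% with an athlete intercept. The last figure is not expected from the algebra, since the covariate cancels from the change contrast. A larger check at r = 0.8 (6,000 runs, team effects taken as fixed) gave 5.5%. I do not count it against the fix.
- **The ICC shift is small beside its sampling error.** True in absolute terms. Section 2.3 already discloses poor precision and says that published ICCs will also inform the next trial. But imprecision is disclosed, whereas this bias is not, and it is avoidable.
- **It is an exploratory pilot, and a fuller plan may specify the covariance.** The study claims no confirmatory inference, which limits the harm. However, the article does not leave the random part open: it lists the terms, and the list falls short of the paragraph's own aim.

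A reader might also infer that team-wide shifts during the season inflate false positives here. They could, but that needs an assumed team-by-wave variance. It is a separate matter, and an athlete intercept would not cure it.

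**Conclusion.** The random part is wrong as written and should be corrected before analysis. It conflicts with the stated aim of handling repeated measures and touches the CIs and ICCs that the plan puts first.

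The size is modest. For r = 0.4–0.8, the condition-by-time SE is about 3–12% too large, and SEs of averaged and athlete-level effects are somewhat too small. In an ICC model without the baseline covariate, the team variance is too high by about 0.01–0.03 of total variance at 20 per team. All of this rests on an assumed exchangeable correlation and balanced data.

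Two stronger readings are not supported. The intervals are not too narrow throughout; for the contrast behind RQ1–RQ3 they are slightly too wide. Nor are the three surveys treated as fully independent: they are independent given team, school and covariates, including the athlete's own baseline.

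**What to change.** In Section 2.9, add a random intercept for student-athlete nested in team, or an unstructured within-athlete covariance across the three waves. Define the team ICC as team variance / (team + athlete + residual variance), estimated from a model without the baseline outcome as covariate, and derive the design effect from it.

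The cost is one model term and one definition. Records must be linked across waves by a stable pseudonymous code. Baseline adjustment already requires that link, and the anonymity wording in Section 2.4 should be checked against it.

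The change does not cure the few-team problem or the one-school-per-arm design. In the simulation without a baseline covariate at a true ICC of 0.05, coverage for the averaged arm difference rose only from 0.84–0.85 to 0.88–0.90. Between-arm intervals should stay labelled descriptive. An interval from the four team-mean changes on 2 df should not be offered as valid between-arm inference either: Section 2.4 makes the school the unit of randomization, and such an interval leaves out school-level variation.
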